# Short-term intensive psychodynamic group therapy versus cognitive-behavioral group therapy in day treatment of anxiety disorders and comorbid depressive or personality disorders: study protocol for a randomized controlled trial

**DOI:** 10.1186/s13063-015-0827-6

**Published:** 2015-07-29

**Keywords:** Anxiety disorders, Depressive disorders, Personality disorders, Psychodynamic psychotherapy, Cognitive-behavioral psychotherapy, Group psychotherapy, Day treatment

## Abstract

**Background:**

Psychodynamic and cognitive-behavioral group therapies are frequently applied in day hospitals for the treatment of anxiety disorders and comorbid depressive or personality disorders in Poland and other Eastern European countries. Yet there is not enough evidence as to their effectiveness in this environment; this study addresses this gap. The aim of the study is to determine the effectiveness of these two kinds of day treatment care consisting of intensive, short-term group psychodynamic and cognitive-behavioral therapy, for patients with anxiety disorders and/or comorbid depressive or personality disorders. Our objectives are to: 1) show the effectiveness of each treatment in a day-care setting relative to the wait-list control group; 2) demonstrate the relative short- and long-term effectiveness of the two active treatments; 3) carry out a preliminary examination of the predictors and moderators of treatment response; 4) carry out a preliminary examination of the mediators of therapeutic change; and 5) compare the impact of both methods of treatment on the outcome of the measures used in this study.

**Methods/Design:**

In this randomized controlled trial, a total of 199 patients with anxiety disorders and comorbid depressive and/or personality disorders will be assigned to one of three conditions: 1) psychodynamic group therapy; 2) cognitive-behavioral group therapy; or 3) wait-list control group. The therapy will last 12 weeks. Both treatments will be manualized (the manuals will address comorbidity). Primary outcome measures will include self-reported symptoms of anxiety, observer-rated symptoms of anxiety, global improvement, and recovery rate. Secondary outcome measures will include the number of pathological personality traits, depression, self-esteem, defense mechanisms, beliefs about self and others, interpersonal problems, object relations, parental bonding, meta-cognition, and quality of life. Measures will be taken at baseline, post-treatment, and at six months following the end of therapy.

**Discussion:**

The rationale is to investigate how effectively anxiety disorders and/or comorbid depressive or personality disorders can be treated in a day hospital setting, typical of the Polish health care system, during a three-month treatment period.

**Trial registration:**

Clinicaltrials.gov identifier NCT02126787, registered on 28 April 2014.

## Background

Group psychotherapy of severe neurotic disorders in a day unit setting has been widely developed in Eastern European countries since the 1960s. This was offered for patients who, due to the disabling intensity of their symptoms, could not function normally and therefore had poor quality of life, and were admitted for three months intensive treatment in day clinic settings. It usually took place five days per week for five to seven hours each day, and took the form of group psychotherapy [57]. This intensive short-term format is still the most available type of psychotherapy, reimbursed by the National Health Service in Poland, where 300 such wards exist today. Every year, approximately 8,000 individuals suffering from anxiety and/or personality disorders are treated in this setting in day clinics in Poland [38]. In spite of its popularity, the effectiveness of psychodynamic and cognitive-behavioral 12-week intensive group psychotherapy treatment for anxiety disorders in a day clinic setting has never been tested or compared with current methodological scrutiny, which has prompted the current research project.

Anxiety disorders are among the most prevalent mental disorders, with a lifetime prevalence of 30 % in the US [42] and 9.9 % in Poland [52], according to a study that used a similar methodology to that conducted in the US. Many studies suggest that in some countries there is a strong comorbidity with personality disorders. A recent meta-analysis of 125 studies [27] demonstrated that the risk of comorbid anxiety disorders and personality disorders varied from 35 to 52 %; the most frequently comorbid disorders are Cluster C personality disorders, as classified by the *Diagnostic and Statistical Manual of Mental Disorders* (DSM-V). Epidemiological studies also show high comorbidity rates for anxiety and depressive disorders, ranging from 40 to 80 % [39, 46]. Data on relationships between comorbid mental disorders and treatment outcomes are inconsistent. Reviews by Reich and Green [64] and Reich and Vasile [65] including 38 studies have shown that comorbid anxiety disorders and personality disorders are negatively related to treatment outcome. However, after analyzing 15 studies, Dreessen and Arntz [21] did not share these conclusions.

It should be noted that the comorbidity of anxiety disorders and personality disorders in the population of neurotic patients treated in day clinics seems to be higher than that reported in other studies. The results of one of our studies show that 125 out of 152 participants (82.3 %) fulfilled the criteria for at least one personality disorder (as assessed by the Structured Clinical Interview for DSM-IV Personality Disorders Questionnaire - II (SCID-II) [76]. The effectiveness of day care has been investigated to a very small degree, especially with regards to its frequent usage [50]. However, difficulties in identifying the basic effective components of the treatment, and the large diversity of the treatment programs make it difficult to generalize the results.

Among the small number of published studies on the effectiveness of psychotherapy in a day care setting, only four were randomized controlled trials (RCTs). Three of those studies compared psychotherapy in day care units to outpatient psychotherapy [2, 19, 80], and one study used a wait-list control group [63]. Tyrer *et al*. [80] found no significant differences between day care and outpatient care for anxiety disorders. Dick *et al*. [19] found a significant difference in improvement of personality disorder pathology in favor of day care. In the first study, the psychotherapy modality was not mentioned, and in the second, eclectic psychotherapy was applied. In another study by Arnevik *et al*. [2], day care treatment (18-week group psychodynamic and cognitive-behavioral psychotherapy) was compared to individual psychotherapy in patients with personality disorders; no significant differences in improvement were observed between the two groups. Piper *et al*. [63] found that day care patients suffering from affective disorders and personality disorders experienced a significant improvement that continued during follow-up after eight months (18-week group psychodynamic psychotherapy), as compared to patients in the wait-list control group. The authors of a Cochrane review of day care versus outpatient care noticed that because of the small number of existing studies, ‘there is only limited evidence to justify the provision of day treatment programs and transitional day hospital care, and no evidence to support the provision of day care centers’ [50]. Existing data are therefore not sufficient enough to justify the use of group psychotherapy in day care, and more high-quality research is needed. The question as to which treatment of the two most widely used forms of therapy, psychodynamic or cognitive-behavioral, is more effective also awaits an answer. These questions are relevant in light of the large expenditures incurred by the national health funds that finance the treatment. They are also important to the issue of health care in Poland, where this type of treatment is very common.

### Objectives

The main objective of the planned research is to evaluate the clinical effectiveness of short-term, intensive, psychodynamic, and cognitive-behavioral group psychotherapy for anxiety disorders and comorbid depressive or personality disorders in day care conditions.

The more specific objectives are to: 1) show the effectiveness of each treatment in a day care setting relative to the wait-list control group; 2) demonstrate the relative short- and long-term effectiveness of the two active treatments; 3) carry out a preliminary examination of the predictors and moderators of treatment response; 4) carry out a preliminary examination of the mediators of therapeutic change; and 5) compare the impact of both methods of treatment on the outcome of the measures used in this study.

## Methods/Design

### Study design

This study is an RCT in which participants will be allocated to one of three conditions: 1) psychodynamic group therapy; 2) cognitive-behavioral group therapy; or 3) the wait-list control group (WL). Participants allocated to the wait list will commence treatment after a 12-week waiting period. The total duration of the study will be three years. Figure 1 shows the trial design. The study protocol, information brochure, and informed consent were approved by the Medical Ethics Committee of Warsaw Medical University (reference number: KB/61/2010).

**Fig. 1 Fig1:**
[figure not shown]
Flowchart of the trial design

### Study center

Both the protocol and the design comprise a part of the research grant given to the II Department of Psychiatry at the Medical University of Warsaw. The study will be carried out at the day unit of the Wola Center for Mental Health at Wola Hospital in Warsaw, which will be used as the clinical setting for the II Department of Psychiatry of the Medical University of Warsaw.

### Participant recruitment, inclusion and exclusion criteria and randomization

Participants with anxiety disorders and comorbid personality disorders will be recruited from an outpatient clinic. Participation is voluntary. Informed consent is given in writing and signed with a personal signature. Participants may withdraw their informed consent at any time, without any consequences for their treatment. Randomization will take place after informed consent has been obtained. Subjects who meet all of the inclusion criteria will be randomized to two modalities of treatments or to the wait list.

Patients from the wait list will continue pharmacological treatment and will take part in monthly supportive consultations. Crisis intervention will be offered when needed. In accordance with the informed consent procedure, patients will not receive treatment in another clinic while waiting for day-treatment care. After the waiting period they will be randomized into two intervention groups.

The inclusion and exclusion criteria are listed in Table 1. The number of excluded patients and the reasons for exclusion will be recorded. The diagnostic criteria are based on the DSM-V system. Initial assessment will be conducted with independent researchers who will not be involved in the further interventions. It will include a pharmacological consultation by a psychiatrist, personality diagnosis with SCID-II [24, 25], and diagnosis of clinical disorders with the Mini International Neuropsychiatric Interview 5^1^ (MINI) [71, 51]. Diagnosis and evaluation for treatment will be carried out during ambulatory sessions. The focus of the treatment is on psychotherapy, but medication will be continued or initiated if necessary during the screening procedure at least four weeks before the beginning of group psychotherapy (stable medical treatments with selective serotonin re-uptake inhibitors or serotonin-norepinephrine reuptake inhibitors, without dose changes during psychotherapy unless necessary). Baseline measurements and final adjustments of pharmacological treatment will be conducted one day before the beginning of therapy. Randomization will take place during the last diagnostic session. Participants will be randomized using random number tables. A recruitment flow chart is presented in Fig. 1. Patients are planned to be enrolled in the study for over a period of three years. Before participating in the study, each patient will be provided with written information about the study and will be invited to give written consent for inclusion. Participants who do not meet the inclusion criteria will be offered suitable alternative treatment options.

**Table 1 Tab1:** Inclusion and exclusion criteria

Inclusion criteria	Current diagnosis of Axis I anxiety disorder (based on the MINI)
	Diagnosis of comorbid personality disorder (based on the SCID II) or depressive disorder (based on the MINI)
	Aged 18 to 65-years-old
	Sufficient knowledge of the Polish language
	Written informed consent from the patient
Exclusion criteria	Organic brain disorder
	Acute substance-related disorders
	Schizophrenia or bipolar affective disorder
	Severe depression (defined as over 26 points on the Beck Questionnaire)
	Cluster A personality disorders
	Current suicidal ideation and a high risk of suicide
	Restricted intellectual capacity
	Serious unstable medical problems or complications
	Concurrent psychotherapeutic treatment

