### Assessments

Patients are subjected to four assessments: 1) at the screening; 2) at baseline after randomization; 3) at the end of the 12-week treatment; and 4) six months after the end of therapy in order to evaluate the longer-term effects of the treatments. Patients in the wait-list group will have one additional assessment at the end of the 12-week waiting period.

Information from the screening will be used to perform stratified randomization and to validate the inclusion and exclusion criteria. Patients will be assessed by independent and trained clinicians who will remain blind to the treatment conditions, and who will not be involved in direct clinical care of any of the patients. Primary outcome measures and secondary outcome measures can be distinguished in this study. The primary outcome measures include self-report symptoms of anxiety, observer-rated symptoms of anxiety, global improvement, and dichotomized diagnosis of anxiety disorder (improved or unimproved). The secondary outcome measures include personality, depression, self-esteem, defense mechanisms, beliefs about self and others, interpersonal problems, object relations, parental bonding, meta-cognition, and quality of life. The following sociodemographic data will be collected: sex, age, marital status, education, past treatments, symptom history, and medication. We will also examine patients’ expectancy toward change and treatment. Some of the variables, such as the presence or absence of a personality disorder, will be treated in exploratory analyses as predictors and moderators of treatment response. The time points of assessment and measures are presented in Table 3.

**Table 3 Tab3:** Instruments at different assessment points

Instrument	Screening	Baseline	End of Treatment	6-Month Follow-up
STAI		X	X	X
HAM-A		X	X	X
CGI-S		X	X	X
CGI-I		X	X	X
M.I.N.I.	X		X	X
SCID-II	X			
BDI-II	X		X	X
OQ-45		X	X	X
SES		X	X	X
DSQ-40		X	X	X
PBQ		X	X	X
IIP		X	X	X
DWM-S		X	X	X
ECR		X	X	X
BORRTI		X	X	X
MCQ		X	X	X
SWLS		X	X	X
CEQ		X		

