### Statistical analysis

All data analyses will be performed using SPSS Statistics software v21.0 (IBM Corporation, Armonk, NY, USA). All randomized patients will be analyzed, including those who stop receiving treatment, on an intention-to-treat (ITT) as well as treatment-completer basis. The multiple imputation method will be used for missing data when appropriate. Analyses of variance with repeated measures (three measurement points: pre, post, and follow-up) will be applied for continuous data (primary outcomes: STAI, HAM-A, CGI-S, and CGI-I; secondary outcomes: BDI-II, OQ-45, SES, DSQ-40, PBQ, IIP, DWM-S, ECR, BORRTI; MCQ, and SWLS). Primary planned comparison is the interaction between the time (pre-to-post and post-to-follow-up change on anxiety) and group variables (CBT versus wait list; PDT versus wait list). Chi-squared tests will be applied for dichotomous data (MINI). Additionally, random effects models for repeated measures will be used. Multiple regression analyses will be applied to test moderators of change that is to show whether each of the interventions is more effective for some groups of patients (interventions, diagnoses, combination of diagnoses and baseline measurements as predictors). Multiple regression analyses will be also applied to search for mediators of change that are theory-specific (for example, changes in beliefs for CBT and changes in defense mechanisms for psychodynamic therapy). We will take into account to what extent the patients were exposed to the intervention by analyzing the dose-effect relationship.

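### The MINI recovery outcome has no baseline reading, so remission before therapy counts as recovery in every arm, diluting the arm differences and raising the reported rates

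*Protocol article*

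**What the plan says.** The Assessments section lists among the primary outcomes the "dichotomized diagnosis of anxiety disorder (improved or unimproved" patient status. The Abstract names the same group of outcomes as "observer-rated symptoms of anxiety, global improvement, and recovery rate".

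Eligibility (Table 1) requires "Current diagnosis of Axis I anxiety disorder (based on the MINI" at screening, so every participant enters with a positive MINI. Table 3 ("Instruments at different assessment points") marks the MINI at screening, end of treatment and six-month follow-up and leaves its baseline cell empty. STAI, HAM-A and CGI-S are marked at baseline.

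On drug treatment, the recruitment section says of the initial assessment: "It will include a pharmacological consultation by a psychiatrist, personality diagnosis with SCID-II", with the MINI in the same list. It then allows that "medication will be continued or initiated if necessary during the screening procedure at least four weeks before the beginning of group psychotherapy", and adds: "Baseline measurements and final adjustments of pharmacological treatment will be conducted one day before the beginning of therapy". Allocation is drawn at the last diagnostic session, and wait-list patients stay on their medication.

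The Statistical analysis section says: "Chi-squared tests will be applied for dichotomous data (MINI"). The planned primary comparisons are each therapy against the wait list. The Sample size section states that the wait list is not available at the third measurement.

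**The concern.** The severity scales are read again just before therapy, so drug response or spontaneous improvement after screening is already in their starting value. The diagnostic outcome has no such second reading. Its only earlier value is the eligibility diagnosis, and at least four weeks of newly started medication may lie between that diagnosis and the first session. A patient who no longer meets criteria by then still enters the trial and, if the remission lasts, is scored as improved.

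Two things are at stake. The first is the power of the test on a primary outcome: patients who had already remitted cannot show an effect of therapy, yet they count as successes on both sides of the comparison. The second is the meaning of the recovery rates. Read within one arm, and above all at six months without a wait list, they mix change before therapy with change during and after it.

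**Working it through.** **Inputs from the article.** 199 patients in three arms, which is about 66 per arm if allocation is equal (199/3 = 66.3; equal allocation is an assumption). Two-sided alpha 0.05. Planned dropout 25%, which leaves about 50 per arm (66 × 0.75 = 49.5). The article states no MINI recovery rate and no power for the MINI, since the sample size rests on continuous outcomes. There is thus no figure of the plan's own to reproduce.

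**Assumptions.** Recovery among patients still ill at the first session (or at the start of the wait) is pT = 50% with therapy and pW = 20% on the wait list. A share r has remitted by that point, is the same in all arms, and stays remitted.

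**Step 1: observed rates.** Observed rate = r + (1 - r) × p. The difference between arms is

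[r + (1 - r)pT] - [r + (1 - r)pW] = (1 - r)(pT - pW).

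This is zero when therapy has no effect and shrinks as r grows. The same holds for CBT against psychodynamic therapy.

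**Step 2: power.** Normal approximation for two proportions: power = Φ[(d - 1.96 × se0)/se1], with d the difference, se0 the pooled and se1 the unpooled standard error. For r = 20% and 66 per arm:
- the rates are 0.60 and 0.36, so d = 0.24
- se0 = √(2 × 0.48 × 0.52/66) = 0.0870
- se1 = √[(0.60 × 0.40 + 0.36 × 0.64)/66] = 0.0844
- power = Φ[(0.24 - 0.1705)/0.0844] = Φ(0.82) = 0.79

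| r | Therapy v wait list | Difference (points) | Power, 66 per arm | Power, 50 per arm |
|---|---|---|---|---|
| 0% | 50% v 20% | 30 | 0.96 | 0.89 |
| 10% | 55% v 28% | 27 | 0.89 | 0.79 |
| 20% | 60% v 36% | 24 | 0.79 | 0.68 |
| 30% | 65% v 44% | 21 | 0.68 | 0.56 |

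At r = 5%, power with 66 per arm is 0.93. With assumed rates of 45% v 15% and 66 per arm, the pattern is the same: 0.97, 0.90, 0.80 and 0.68 for r = 0, 10, 20 and 30%.

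**Step 3: a benchmark.** If it were known exactly who was still ill at the first session, a test among those patients (66 × (1 - r) per arm, 50% v 20%) would have power 0.94, 0.91 and 0.87 for r = 10, 20 and 30%. Adjusting for baseline severity would recover part of this gap. How much depends on how well HAM-A and CGI-S track diagnostic status, which the article does not tell.

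**Step 4: within-arm rates.** The share of recovered therapy patients who had remitted before the first session is r/[r + (1 - r)pT]: 0.10/0.55 = 18%, 0.20/0.60 = 33% and 0.30/0.65 = 46%.

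**The case against.** The strongest defence is that recovery is credited to therapy only through the randomised contrast. Allocation comes at the end of the diagnostic phase and the wait list stays on medication, so remission before therapy is shared equally in expectation. Taking the eligibility diagnosis as the reference is then a valid, if less precise, choice. This stands. A reader might infer that pre-therapy remission is booked as an effect of therapy against the wait list, but Step 1 shows that the planned contrast moves towards zero, not in favour of therapy.

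Three further limits also stand:
- The article does not say whether the MINI comes before or after the drug start within screening, and patients already on stable medication have no new drug response to count. That r is large therefore cannot be shown. On the assumed rates with 66 per arm, power falls below 0.80 only from about r = 20%.
- The article does not spell out how improved is scored. Reading it as loss of the diagnosis follows from the Abstract's term for recovery.
- The 50-per-arm column suits the completer analysis. The intention-to-treat analysis keeps all randomised patients.

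A reader might also infer a bias favouring therapy through unequal intervals, for example if the wait starts at randomisation while therapy patients wait for a closed group to fill. If r were 10% in a therapy arm and 5% on the wait list, with no therapy effect and 15% recovery among those still ill, the false difference would be 0.235 - 0.1925 = 4.3 points. But the article does not state when the wait-list clock starts, so this is conjecture.

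At six months the stated objective is the relative effect of two randomised therapies, and shared early remission does not bias that contrast either. The objection does not answer the loss of power or the mixed content of the absolute rates.

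**Conclusion.** The point holds as one of efficiency and labelling on a primary outcome. It is not a bias in the comparison of therapy with wait list, or of one therapy with the other. Those differences are diluted by (1 - r). Under the assumed 50% v 20% with 66 per arm, a 30-point difference becomes 27, 24 or 21 points for r = 10, 20 or 30%, and power drops from 0.96 to 0.89, 0.79 or 0.68. Within-arm and six-month recovery rates include change before therapy: 18% to 46% of the recovered therapy patients over the same range of r. The sizes rest on r and on recovery rates that the article does not give, and on early remission lasting. The missing baseline MINI, the permitted drug start before therapy and the unadjusted test are stated in the article itself.

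**What to change.** In the Statistical analysis section, replace the chi-squared test for the MINI with a logistic regression of recovery on arm, over all randomised patients, adjusted for baseline HAM-A and CGI-S. Report recovery rates as counted since screening, including change before therapy. This uses data already scheduled and costs only a change of wording. Adjustment recovers part of the lost power but does not take early remitters out of the rates, which is why the label is needed as well.

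Optionally, repeat the MINI anxiety modules at the existing baseline visit in all arms. Use the result as a covariate, or for a sensitivity analysis among patients who still meet criteria. Keep the all-randomised analysis primary: baseline follows randomisation, so restricting the main denominator there would be a post-randomisation exclusion. The cost is a somewhat longer baseline visit.

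### Final medication adjustments come after randomization, on a day tied to the start of therapy, so drug treatment can differ by arm in the wait-list comparison

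*Protocol article*

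**What the plan says.** The section on recruitment, eligibility and randomization sets a medication run-in: "medication will be continued or initiated if necessary during the screening procedure at least four weeks before the beginning of group psychotherapy". Treatment with SSRIs or SNRIs is then to be stable, "without dose changes during psychotherapy unless necessary". The same section adds: "Baseline measurements and final adjustments of pharmacological treatment will be conducted one day before the beginning of therapy".

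On the order of steps, that section says "Randomization will take place during the last diagnostic session", and the Assessments section lists the second assessment as "2) at baseline after randomization".

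For the wait list, the rule is: "Patients from the wait list will continue pharmacological treatment and will take part in monthly supportive consultations". The Assessments section adds: "Patients in the wait-list group will have one additional assessment at the end of the 12-week waiting period". The only blinding described is of the assessors, "who will remain blind to the treatment conditions, and who will not be involved in direct clinical care of any of the patients".

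Under Statistical analysis, the primary planned comparison is the time-by-group interaction on anxiety, for each therapy against the wait list.

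**The concern.** A four-week run-in on stable medication is meant to keep drug effects out of the trial window. A final adjustment on the day before therapy works against this, because whatever it does to anxiety happens during the following 12 weeks. It breaks no literal clause, so the two medication sentences are in tension and do not strictly contradict each other.

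The order of steps is the more serious matter. The adjustment follows allocation, and its date is defined by a start of therapy that the wait-list arm does not share. If adjustments differ between arms in number or kind, the difference is either counted as a psychotherapy effect or hides one. Intention-to-treat analysis does not remove it, since it keeps patients in their arms but does not separate two treatments that both differ by arm.

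**Working it through.** **Order of steps**

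1. Randomization is at the last diagnostic session (recruitment section).
2. Baseline follows randomization (Assessments section).
3. Final medication adjustment shares the baseline day, one day before therapy (recruitment section).
4. Hence the adjustment follows allocation.

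**Is the arm known?** The protocol does not say that the prescriber is told the arm, so this is an inference. It is a strong one: a patient seen the day before starting group therapy is plainly not on the wait list, and the stated blinding covers assessors outside clinical care, not prescribers.

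**What happens on the wait list?** These patients need a baseline before the wait, because their assessment at the end of it is described as additional. Two readings of the adjustment rule are possible.

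- *The day before therapy means the end of their wait.* The therapy arms are then adjusted at the start of the comparison window and the wait list is not. The between-arm difference equals the whole share adjusted in the therapy arm.
- *It means their own baseline.* The text does not say so, and the dose limit, worded for psychotherapy, still does not cover the waiting period.

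Contact with prescribers may differ too: Table 2 puts a psychiatrist group consultation in the therapy schedule, while the wait list has monthly supportive consultations.

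**Size.** The protocol gives no adjustment rate and no drug effect, so both are assumed.

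- Difference in share adjusted, therapy minus wait list: -20 to +20 percentage points.
- Effect of an adjustment on anxiety over 12 weeks: 0.1 to 0.5 SD.
- Planned effect against wait list: 0.58 (Sample size calculation).
- Completers per arm, assuming equal allocation: 199 × 0.75 / 3 = 49.75.
- Standard error of the difference in SD units, without baseline adjustment: √(2/49.75) = 0.201.

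Bias = (difference in share adjusted) × (effect of an adjustment). Its sign follows the sign of the difference.

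| Difference in share | Effect (SD) | Bias (SD) | Share of 0.58 | Bias / SE | Two-sided error at nominal 5% |
|---|---|---|---|---|---|
| 0 | any | 0 | 0% | 0 | 5.0% |
| 0.10 | 0.1 | 0.01 | 1.7% | 0.05 | about 5% |
| 0.10 | 0.5 | 0.05 | 8.6% | 0.25 | 5.7% |
| 0.20 | 0.5 | 0.10 | 17.2% | 0.50 | 7.9% |

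The last column is Φ(-1.96 + b) + Φ(-1.96 - b), with b the bias in standard errors. For b = 0.50 this is Φ(-1.46) + Φ(-2.46) = 0.079.

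**Sensitivity to the assumptions.** With differences of 10 to 30 points and effects of 0.3 to 0.5 SD, the bias is 0.03 to 0.15 SD. The error rate is then 5.3% to 12.1% with 53 per arm (159/3) and 5.3% to 13.8% with 66 per arm (about 199/3).

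**The case against.** The strongest defence is that the main drug exposure is settled before allocation. A psychiatrist's consultation belongs to the initial assessment, medication is started or continued during screening, and future wait-list patients go through the same steps. Against that background a final adjustment may be no more than a closing check on an established regimen. Wait-list patients continue their medication and agree not to be treated in another clinic. Visit-level prescribing detail could also reasonably sit in the full protocol, which a journal article condenses. The magnitudes are assumed throughout, and the larger ones need a sizeable imbalance together with a generous effect for a late change.

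Part of this stands. The screening steps do limit how much is left to adjust, which favours the lower end of the range, and the figures show sensitivity to assumptions without estimating anything. Silence about wait-list prescribing would not be a finding on its own. But the point does not rest on silence: the stated schedule, followed as written, puts a co-intervention after open allocation and ties both it and the dose limit to therapy. Earlier equal steps do not equalize a later unequal one.

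It is also fair that therapy runs in closed-ended groups, so a patient whose medication has to settle before the draw could miss a group start.

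**Conclusion.** The concern holds. The order of steps is explicit in the article. That the arm is known at the adjustment is inferred from the open design and the absence of any prescriber blinding. That the adjustment concerns SSRIs or SNRIs is the natural reading, since those classes are named in the stability rule just before it.

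The exposure affects both primary comparisons with the wait list. Its direction is unknown and its size rests on assumption: at most 0.10 SD either way over the main range considered, and nil if all arms are adjusted alike. The comparison of psychodynamic with cognitive-behavioral therapy is less exposed, because those arms share the same anchor date and dose rule. A possible bias of this size does not undermine the trial, but it is easily avoided and should be fixed.

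**What to change.** - Complete all planned medication adjustments before the allocation is drawn, ideally at least four weeks before baseline.
- Hold doses fixed in all three arms over their 12 weeks, with the existing exception for clinical need, timed from randomization or baseline and not from the start of therapy.
- Record each later change with date and reason, and report changes by arm.
- Keep the intention-to-treat analysis primary, and exclude no patient or data because of a medication change.

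The cost is protocol wording and moving one step ahead of the draw; medication is already among the data collected. Scheduling of the last pharmacological consultation becomes slightly less flexible, and patients whose medication is started or changed at screening are randomized later, which may occasionally mean waiting for the next closed group. The article was published in July 2015 with recruitment anticipated from September 2015, so on its own timeline the change could precede enrolment.
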